### Recruitment of older persons

Participating GPs recruited older persons to the project in four steps (Figure 1). Firstly, all practices generated lists of their older patients. The age cut-off for listing patients was based on the country-specific age used for planning and delivery of services to the elderly. In London and Solothurn, an age cut-off of 65 years was selected, in Hamburg a cut-off of 60 years. In a second step, practices were asked to exclude patients meeting the following exclusion criteria: needing human assistance for performing basic activities of daily living or living in a nursing/residential home (in Germany, nursing care according to the German long-term care insurance system); cognitive impairment (i.e. possible dementia, equivalent to a Mini Mental Status score of 24 or less [9]; terminal disease; and/or inability to speak the regional language. In a third step, GPs sent an invitation letter to all individuals remaining on the list. The invitation included an information sheet describing the planned project, the Pra (Probability of repeated admissions) questionnaire [10,11], and a self-administered question on self-perceived need for human help in basic activities of daily living [12]. Patients were asked to return the completed questionnaire if they were interested in participating in the study, and to give informed consent according to the policies of the responsible institution. In London and Solothurn patients were asked to complete and return a written consent form. In Hamburg patients were informed that by returning the questionnaire they agreed to participate in the study. All patients were informed that they could withdraw from the project without negative impact on their care. In a fourth step, persons reporting a need for human assistance in performing basic activities of daily living in the questionnaire, those returning an incomplete Pra questionnaire, and those declining participation (by not returning the brief questionnaire or by returning the questionnaire with an explicit statement of refusal) were excluded from the study. The remaining persons were included in the final list of participants in the study.

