At all sites, survival status and move into permanent long term care among non-responders at follow-up was obtained from GPs, and if available from registers in participating regions. Move into permanent long-term care was defined as living in a nursing home in London and Solothurn, and in Hamburg as requiring nursing care according to the German long-term care insurance system.

At the end of the follow-up period (London and Hamburg, at one-year follow-up, Solothurn at two-year-follow-up), participating GPs and other health personnel involved in the HRA-O intervention, received a structured, uniform questionnaire for written feed-back on the project.

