### Statistical analyses

All analyses follow an a priori analytic plan. The primary outcomes are health behaviour and preventative care use, as listed in Table 2[2,5,21-25]. Secondary outcomes include mortality, need for long-term care (living in nursing home, or designated as requiring long-term care according to the German long-term care insurance system), and self-reported information on health status (vision, hearing, self-perceived health status, pain, depressive symptoms, falls history, and functional status).

To conduct planned sensitivity and subgroup analyses of primary outcomes, two composite scores will be created: one for adherence to positive health behaviour, and one for use of recommended preventative care. The percentage of health behaviour domains (Table 2) for which the patient showed a positive level of performance, and the percentage of recommended preventative care measures (Table 2) the patient had used will be determined. We will impute composite scores for individuals in whom ≤ 20% of the required outcome data were missing. Imputation will be conducted as follows: based on available baseline variables multiple linear regression models (using the complete base-line information and household status) will be derived in the subset of persons with complete data on outcomes, and subsequently, these models will be used to impute composite score estimates in persons with missing information.

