Outcome analyses of the randomised controlled study will be conducted for each site separately in keeping with the inter-site variations of reinforcement methods. The main analyses will compare primary and secondary outcomes between intervention and control groups at follow-up. In these analyses, the fact that participants living in the same household were allocated to the same group will be taken into account by adding the information on household membership to generalised estimating equations (GEE) models [26,27]. Subgroup analyses will be used to evaluate whether the intervention effects differ between predefined subgroups of the population. Firstly, outcomes will be compared between older persons at high risk (Pra > 0.28) and those at low risk (Pra ≤ 0.28) for hospital use [10,11], based on the hypothesis that this type of intervention might have greater positive effects in persons at low risk [28]. Second, for the randomised study in Hamburg and Solothurn, an additional analysis will be carried out to evaluate the independent effects of the site-specific reinforcement on primary outcomes: multivariate regression analyses will be conducted using the composite scores as outcome variables, and participation status in the reinforcement as an independent variable, controlling for intervention allocation status and available participant base-line characteristics. Finally, sensitivity analyses will be conducted to evaluate for potential bias resulting from missing outcome data. First, all analyses will be repeated by adjusting GEE models for base-line age, gender, self-perceived health and number of physician visits reported. Second, primary outcome analyses will be repeated by using with composite scores of health behaviour and use of preventative care which will be derived from imputed outcome estimates in persons with partially missing information.

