We will also evaluate changes in preventative care use, health behaviour, and health status between baseline and the one-year follow-up among persons in the intervention group. This analysis will be possible because persons in the intervention group received the HRA-O questionnaire both at base-line and at one-year follow-up. This analysis will adjust for household membership and base-line variables (age, gender, self-perceived health status, health care use prior to base-line). These pre-post analyses will be restricted to the intervention group since primary outcomes were not measured in the control group at baseline.

Outcome analysis of data from the concurrent comparison group will include a comparison of primary and secondary outcomes between the intervention group and the concurrent comparison group. The primary analysis will be a comparison of primary outcomes adjusted for base-line factors.

Categorical and binary outcome data will be analysed using chi-square tests; continuous outcome data will be compared using t-tests if normally distributed, Mann-Whitney U test if skewed. Number of physician visits will be analysed with ordered logistic regression models. To allow for within-household clustering, Generalised Estimating Equations (GEE), assuming an exchangeable correlation structure, will be used to analyse all outcomes [27]. Data will be analysed using the SAS programme [29].

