An additional limitation of the PRO-AGE study is the fact that the study was not powered to measure the effects of the intervention on the prevention of functional decline and nursing home admissions. However, it is appropriate, as a first step, to conduct a study for identifying effective intervention methods in the short-term, and in a second step, to plan new studies to evaluate the effects of an optimised intervention strategy over longer time periods.

A further limitation of this study is the possibility of contamination effects. Patients allocated to control groups may have benefited from the intervention because they received usual care from their GPs who had received special training and were involved in the intervention (Table 1). In anticipation of this problem, the study design includes outcome evaluations in a parallel concurrent comparison group with patients receiving care from physicians who had not received training in preventative geriatric medicine. A comparison between intervention and concurrent comparison group is expected to give an estimate of treatment effects without contamination bias, but is limited due to potential selection bias. In fact, there were some small but significant differences in base-line characteristics between participants of the intervention and concurrent comparison groups. Among other factors, this might be related to the fact that the number of clusters randomised was only 4 in London, and 3 in Solothurn. To address this limitation, the analyses comparing outcomes between intervention and concurrent comparison groups will adjust for base-line characteristics.

In conclusion, recruitment of study participants to this project was successful, and base-line findings confirm the success of the randomisation and the comparability of base-line characteristics between intervention and control groups. The a priori analytic plan which examines intervention effects takes into account the described limitations, and includes sensitivity analyses evaluating potential sources of bias. Furthermore, the database containing cross-sectional and longitudinal information on multiple health risks in older people will also be useful for refining existing instruments or methods of risk prediction in older people.

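### Long-term care is defined by a current status at follow-up and compared apart from death, so a survival difference between arms could distort the comparison

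*Protocol article*

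**What the plan says.** Under Data collection, the article first speaks of an event obtained together with vital status: "survival status and move into permanent long term care among non-responders at follow-up was obtained from GPs", and from registers where available. It then defines that event by a state. For two sites, "Move into permanent long-term care was defined as living in a nursing home in London and Solothurn"; for the third, it is defined "in Hamburg as requiring nursing care according to the German long-term care insurance system".

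Under Statistical analyses the state wording returns, beside a separate mortality outcome: "Secondary outcomes include mortality, need for long-term care (living in nursing home, or designated as requiring long-term care". On the comparison, "The main analyses will compare primary and secondary outcomes between intervention and control groups at follow-up". On method, "Categorical and binary outcome data will be analysed using chi-square tests", with GEE to allow for households. The article does not combine death with care, does not treat death as a competing event, and does not say how a person who moved and then died is counted.

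Two further statements bear on the size of the problem. Patients were excluded at entry for "needing human assistance for performing basic activities of daily living or living in a nursing/residential home", so participants were meant to be living outside institutional care. The Discussion concedes that "the study was not powered to measure the effects of the intervention on the prevention of functional decline and nursing home admissions".

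**The concern.** A state that only a living person can hold is being compared between randomised arms, while death is handled elsewhere. This has two consequences.

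- A move into care that ends in death before follow-up drops out of the care outcome.
- If the intervention keeps frail people alive, some of them will be in care at follow-up. The intervention arm then shows more care because it shows fewer deaths.

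In the second case an intervention that does good on one outcome would look harmful on the other. The Background gives preventing or delaying disability as the public-health motive, so readers will look at the care result even though it is secondary. The Discussion's caveat about power warns of imprecision. It does not warn that the direction of the estimate may depend on survival.

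**Working it through.** **The plan's own figure.** The article gives no rate, effect or sample size for death or long-term care. Its only calculation concerns the primary outcomes. Taking 20% against 26%, two-sided 0.05, 80% power, a continuity correction and 20% drop-out gives 1007 per group at 1:1 (stated: 1000) and 745 and 1490 at 1:2 (stated: 763 and 1525). It reproduces to within 3% but does not bear on this point.

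**Inputs.** Arm sizes (intervention/control) are from Table 4: London 1240/1263, Hamburg 878/1702, Solothurn 874/1410. All event rates below are assumptions.

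**Check 1: a survival benefit and nothing else.** Let d be the control death rate, l the control share in care at follow-up, and f the share of spared people who are in care. Deaths fall by 30%.

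- Care ratio = (l + 0.3·d·f) / l
- Dead-or-in-care ratio = (0.7·d + l + 0.3·d·f) / (d + l)

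Central case (d = 3%, l = 1.5%, f = 25%): 0.3 × 3% × 25% = 0.225%.

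- Care ratio = 1.725/1.5 = 1.15
- Combined ratio = (2.1 + 1.725)/4.5 = 0.85

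Over d = 2–4%, l = 1–2% and f = 10–40%:

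- The care ratio runs from 1.03 (2%, 2%, 10%) to 1.48 (4%, 1%, 40%).
- The combined ratio runs from 0.78 (4%, 1%, 10%) to 0.91 (2%, 2%, 40%).

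In people, 0.225% of the intervention arm is 2.8 in London and 2.0 in each of Hamburg and Solothurn.

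**Check 2: equal moves, different deaths after moving.** Let a share m of each arm move, and let q be the share of movers who die before follow-up. The ratio of those alive in care is (1 − q_int)/(1 − q_ctl), whatever m is. With m = 5% and 4% deaths among the rest:

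| q control | q intervention | Alive in care, control | Alive in care, intervention | Ratio |
|---|---|---|---|---|
| 30% | 30% | 3.50% | 3.50% | 1.00 |
| 30% | 20% | 3.50% | 4.00% | 1.14 |
| 30% | 15% | 3.50% | 4.25% | 1.21 |
| 40% | 20% | 3.00% | 4.00% | 1.33 |

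Using survivors as the denominator changes little (1.14, 1.21 and 1.32 in the last three rows). In every row the ever-moved ratio is 1.00, and dead-or-in-care is 5% + 95% × 4% = 8.8% in both arms. If moves truly fall by 10% and deaths follow the third row, the status ratio is 0.9 × 0.85/0.70 = 1.09, so the direction reverses.

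**Check 3: precision.** Power = Φ(δ/SE − 1.96) + Φ(−δ/SE − 1.96), with unpooled SE and households ignored. Take London, with 1.5% in care, 3% deaths, and an intervention that lowers only care, by 30%.

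- Care alone: 1.05% against 1.5%, δ = 0.45%, SE = 0.448%, power 17%.
- Combined: 4.05% against 4.5% (ratio 0.90), δ = 0.45%, SE = 0.808%, power 9%.

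If deaths also fell by 30%, the combined outcome (3.15% against 4.5%) would have about 42% power in London. That gain comes from assuming an effect on death.

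**The case against.** The strongest reply is that the article never says a mover who died is dropped. It calls the variable a move, and the state wording may only say what counts as permanent care at each site. Hamburg's criterion is an insurance designation, which could have been made before death and still be counted. Counting rules of this kind often sit in an analysis plan that is not shown here. This stands in part: the loss of such cases follows from the literal wording but is not declared. A reader might infer that the plan knowingly discards them, and the documents do not support that. They do leave two readings that give different event counts. Deaths themselves are not lost, since they are counted under mortality.

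The second reply is size. The distortion needs a sizeable survival difference within one year (two in Solothurn), in people screened as non-disabled, without dementia and not terminally ill. In the central case the London ratio of 1.15 rests on about 21.4 against 18.9 expected events, with an approximate 95% interval of 0.62 to 2.12. No one could properly claim harm from that. This stands, and it limits the point to a modest one.

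Third, a reader might infer that a combined outcome should replace long-term care because it has more events and so more power. Check 3 shows why that fails: the gain depends on deaths falling too, and where only care need falls the power is roughly halved.

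**Conclusion.** The point holds in a limited form. On the literal definition, the care comparison depends on survival and could point the wrong way. Under the assumed rates, the apparent ratio is 1.03 to 1.48 from a 30% fall in deaths alone, or 1.14 to 1.33 from fewer deaths among movers. If survival among frail people does not differ between arms, there is no distortion.

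It is probably small at one year, and larger at two years in Solothurn, where there is more time for death to follow a move. The outcome is secondary and admittedly unpowered, and conclusions on health behaviour and preventative care use are untouched. The documents do not show that a distortion will occur, nor that the intervention affects mortality.

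**What to change.** 1. Keep mortality and long-term care as separate secondary outcomes, with the site-specific care definitions.
2. State that any move into care, or care designation in Hamburg, before follow-up is an event whether or not death followed, wherever the GP or register information shows it. This settles the two readings and removes the distortion in Check 2.
3. Add dead or in long-term care at follow-up as a companion secondary outcome, analysed with the same household GEE in all randomised persons with known status. This is needed because step 2 does not deal with people who, without the intervention, would have died before any move.
4. Interpret the care result only together with mortality and the combined outcome.

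The cost is one counting rule, one derived variable and a few sentences. Vital and care status are already sought for non-responders at every site, so no new data collection is needed, although the date or fact of a move before death may not always be recorded. The downside is that the combined outcome mixes death with care need and has less power than care alone if only care need is affected, so it should not be presented as a gain in power.

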### Sample size/power calculation

We calculated the required sample size for detecting, at a two-sided significance level of 0.05 and with a power of 80%, a postulated 30% difference in positive health risk behaviour or preventative care use in the intervention group as compared to controls at the one-year follow-up. For this calculation, a prevalence of positive behaviour or preventative care use among controls of 20% was assumed, based on pilot data in a comparable sample of community-dwelling older persons [6]. Based on a 1:1 randomisation ratio and a predicted drop-out rate at one year of 20%, the required sample size was 1000 persons per group. In Hamburg and Solothurn, due to limitations in resources available for offering the intervention (group sessions, home visits), a randomisation rate of 1:2 was preferable. Based on a 1:2 randomisation rate, and on the same drop out rate, the required sample size was 763 persons in the intervention group and 1525 persons in the control group.

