**Preventative care use [21]**		
-Blood pressure	Self-report: blood pressure control in previous year	Medical record: blood pressure control in previous year
-Breast cancer screening	Self-report: mammography in previous 2 years	n.a.
-Cholesterol	Self-report: cholesterol measurement in previous 5 years	Medical record: cholesterol measurement in previous 5 years
-Colon cancer screening	Self-report: faecal occult blood test in previous year	Medical record: faecal occult blood test in previous year
-Dental care	Self-report: dental check in previous year	n.a.
-Diabetes screening	Self-report: blood glucose measurement in previous 3 years	Medical record: blood glucose measurement in previous 3 years
-Hearing examination	Self-report: hearing check-up in previous year	n.a.
-Influenza immunisation	Self-report: influenza vaccination in previous year	Medical record: influenza vaccination in previous year
-Pneumococcal immunisation	Self-report: pneumococcal vaccination (ever)	Medical record: pneumococcal vaccination (ever)
-Vision examination	Self-report: vision check-up in previous year	n.a.

PRO-AGE: PRevention in Older people – Assessment in GEneralists' practices

n.a. denotes not available

In Solothurn, in addition to the one-year follow-up, a two-year follow-up was conducted among persons in the randomised study (not in the concurrent comparison group). Health behaviour outcome data were collected using a two-page questionnaire based on the Healthtrac questionnaire [2]. In addition, older persons were asked for their self-perceived health status, and for need for help in basic activities of daily living. Non-responders or those who returned incomplete questionnaires, were contacted by telephone, or visited at home, and a trained research assistant, blinded for group allocation, attempted to obtain missing information. Selected preventative care measures (those mainly offered by GPs, and not by specialists, in the Swiss health care system) and selected health measurements (most recent values of blood based measurement, serum cholesterol, and serum glucose) were obtained from a review of primary care medical records. This abstraction of medical records was conducted by practice assistants based on an alphabetised list of participating patients blinded for group allocation.

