## Discussion

To our knowledge this is the first randomised study of a HRA-O intervention conducted in Europe. As shown in this paper, the PRO-AGE project was successful in recruiting the large number of older persons required to evaluate – with adequate statistical power – the effects of a HRA-O intervention on health behaviour and use of preventative care. The PRO-AGE project has additional strengths. The HRA-O intervention was implemented in three sites in different countries, with different health care systems, different languages and different cultural backgrounds. Furthermore, each site implemented an additional specific reinforcement of the HRA-O. Thus, this study can evaluate the effects of HRA-O with varying forms of reinforcement in a broad range of older persons. Finally, based on the planned risk-stratified analyses using the Pra questionnaire, it will be possible to evaluate whether effects are more positive in persons at low risk, as compared to persons at high risk, as suggested by recent research evidence [28].

The PRO-AGE project has several limitations. Firstly, one-year outcome analysis is based on self-reported information alone, and there is no systematic information from direct patient observation, no cost data, and only limited information from medical records available for this analysis. However, since we used validated instruments to obtain information on a broad range of health-related measures, the study will provide valid estimates on the effects of HRA-O on health behaviour, preventative care use, and health status in older persons.

Second, outcome data will not be available for a part of the study participants due to missing data. Due to budgetary constraints it was not feasible to implement a reminder system or use some other mechanism for obtaining outcome data from persons who did not respond or only partially responded to the one-year follow-up questionnaire. The magnitude of this limitation will depend on the percentage of missing information among study participants at the three study sites. The potential impact of missing data will be evaluated in statistical sensitivity analyses.

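### The sample sizes reproduce for outcomes defined in all participants, but at the plan's own inputs they do not give the stated 80% power for mammography, which in practice applies only to women

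*Protocol article*

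**What the plan says.** The section on sample size and power makes one calculation. It is set "at a two-sided significance level of 0.05 and with a power of 80" per cent, for "a postulated 30% difference in positive health risk behaviour or preventative care use in the intervention group as compared to controls", where "a prevalence of positive behaviour or preventative care use among controls of 20% was assumed". For equal allocation the result reads: "Based on a 1:1 randomisation ratio and a predicted drop-out rate at one year of 20%, the required sample size was 1000 persons per group". For 1:2 allocation it gives 763 intervention and 1525 control participants. The count is of persons, with no allowance for an outcome that concerns one sex.

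Table 2 lists the one-year primary outcomes: six health behaviour items and ten preventative care items. The breast cancer screening item is "Self-report: mammography in previous 2 years". The section on statistical analyses makes all Table 2 items primary and analyses each site on its own.

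The Discussion describes the project as "successful in recruiting the large number of older persons required to evaluate – with adequate statistical power – the effects of a HRA-O intervention". That statement names both outcome domains, behaviour and preventative care, and makes no exception.

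**The concern.** A power figure carries over from the whole cohort to a single outcome only if that outcome can be observed in the whole cohort. Mammography cannot. Table 4 shows that 54.6% to 63.3% of each randomised arm are women, so the usable sample for this outcome is a little over half of what the calculation assumes. Because each site is analysed separately, pooling cannot make up the difference.

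The loss of power comes from who can contribute to the outcome. It exists even if follow-up is exactly as planned. A reader who takes the 80% and the Discussion's statement at face value could give a non-significant mammography result more weight as evidence of no effect than the plan's own inputs justify.

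**Working it through.** **Inputs.** From the sample size section: two-sided α = 0.05, power 80%, control rate 20%, a 30% difference, 20% loss. From Table 4, women (intervention/control): London 686/689, Hamburg 540/1077, Solothurn 497/796. All randomised: 1240/1263, 878/1702, 874/1410.

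**Step 1: reproduce the plan's figures.** Read the 30% as relative: 20% × 1.3 = 26%. For equal arms,

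n = [1.96·√(2p̄(1−p̄)) + 0.84·√(p₁(1−p₁) + p₂(1−p₂))]² / (p₁−p₂)², with p̄ = 0.23,

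gives 772 per arm, or 805 with the Fleiss continuity correction. Dividing by 0.8 gives 965 or 1007; the plan states 1000. At 1:2 the corrected formula gives 596/1192 evaluable, hence 745/1490 randomised; the plan states 763/1525. The corrected results are within 3% of the stated ones. Other readings of the 30% do not fit: 20% vs 14% needs 809 per arm (corrected), and 30 percentage points needs 39 evaluable per arm. So 20% vs 26% is the planned effect, and the stated sizes are sound for an outcome measured in everyone.

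**Step 2: power formula.**

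Power = Φ[(|p₁−p₂| − c − 1.96·s₀)/s₁]

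- s₀ = √(p̄(1−p̄)(1/n₁+1/n₂)), with p̄ the average rate weighted by arm size
- s₁ = √(p₁(1−p₁)/n₁ + p₂(1−p₂)/n₂)
- c = 0 uncorrected, or ½(1/n₁+1/n₂) with continuity correction

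Example, London women after 20% loss: 686 × 0.8 = 548.8 and 689 × 0.8 = 551.2. Then s₀ = 0.02537, s₁ = 0.02532, and (0.06 − 1.96 × 0.02537)/0.02532 ≈ 0.405, so power is 65.7%.

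**Step 3: results at 20% vs 26%** (uncorrected; continuity-corrected in brackets).

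| Site | All, 20% loss | Women evaluable, 20% loss | Women, 20% loss | Women, no loss |
|---|---|---|---|---|
| London | 89.1% (88.1%) | 549/551 | 65.7% (63.1%) | 75.3% (73.3%) |
| Hamburg | 87.0% (85.8%) | 432/862 | 68.5% (66.0%) | 77.8% (75.9%) |
| Solothurn | 84.5% (83.1%) | 398/637 | 61.4% (58.5%) | 70.9% (68.6%) |

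Outcomes that apply to everyone exceed 80% at every site. Mammography falls short at every site, even with no loss.

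**Step 4: dependence on the control rate.** The documents give no mammography rate, so it is varied here as an assumption. Power in women with the same 30% relative difference and 20% loss, uncorrected:

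| Control rate | London | Hamburg | Solothurn |
|---|---|---|---|
| 10% | 34% | 37% | 32% |
| 20% (plan) | 66% | 69% | 61% |
| 25% | 79% | 81% | 74% |
| 28% | 85% | 87% | 81% |
| 30% | 88% | 90% | 85% |
| 40% | 98% | 98% | 97% |

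All three sites reach 80% from a control rate of about 28% (about 29% with continuity correction).

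**The case against.** The strongest case against has four parts.

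1. *The 20% is a generic planning rate, not a mammography rate.* This stands. A reader might infer that the trial is underpowered for mammography, or that it would miss a real effect about one time in three. The documents do not support that: at a control rate of about 28% or more, with the same relative difference, every site reaches 80%, and at 10% power is far lower than the figures at 20%. True power is simply not known.

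2. *Nothing is miscalculated.* This also stands. A reader might infer an arithmetic error in 1000 or 763/1525, and there is none. Nor does a direct comparison of the number of women with those sizes prove the point alone. Solothurn's allocation averaged 1:1.6, for which no requirement is stated, and its full control arm (1410) is also below 1525 although whole-cohort power there is 83–85%.

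3. *The article claims power for two broad domains, not for each item, and one representative calculation cannot guarantee 80% for 16 outcomes with different prevalences.* This is fair in part. But differing prevalences are a matter of assumption, whereas the restricted denominator is known from Table 4 and lowers power at any assumed rate. The Discussion's statement covers preventative care use without exception.

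4. *A condensed article may leave item-level power to its analytic plan.* It may. The point does not rest on missing detail: the calculation, the number of women and the adequacy statement are all published here, and the third does not follow from the first two for this outcome.

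The article also does not say that mammography is analysed in women only. That follows from the nature of the test.

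**Conclusion.** The concern holds in a limited form. The stated 80% does not carry over to the primary outcome mammography at the inputs to which it is attached. There, power is about 63–66% in London, 66–69% in Hamburg and 58.5–61% in Solothurn.

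This rests on women being the denominator, on the 30% being relative (the only reading that reproduces the stated sizes), on 20% loss applying equally to women in both arms, and on ignoring household clustering, which the article's calculation does not mention either. It affects one of 16 one-year primary items. For outcomes defined in the whole cohort, the adequacy statement is right at the plan's inputs. The point is minor and concerns how the power is described.

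**What to change.** - In the sample size section, state that the 80% applies to outcomes defined for all participants.
- Give power for mammography by site on the number of women, with the assumed control rate stated and a range shown. The figures at 20% should not stand alone as if 20% were a known mammography rate.
- In the Discussion, limit the adequate-power statement to outcomes that apply to the whole cohort.

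The cost is wording only. No participants are added and no analysis changes. One figure becomes less favourable for one primary outcome at the planning rate.
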